## Abstract

Tuberous sclerosis complex (TSC)-associated neuropsychiatric disorders (TAND) affect ≈90% of individuals with TSC and significantly reduce their quality of life (QoL). However, there are limited studies assessing pharmacotherapy for TAND. A plant-derived highly purified pharmaceutical formulation of cannabidiol (CBD; Epidiolex^®^/Epidyolex^®^ oral solution) is approved for seizures associated with TSC. Anecdotal evidence also suggests psychiatric, neuropsychological, and behavioral benefits of CBD. EpiCom (**Epi**lepsy **Com**orbidities; NCT05864846; EU-CT, 2023-507426-17), a multicenter, open-label, phase 3b/4 study, with hybrid decentralized approach, was designed in collaboration with patient advisory groups and healthcare professionals to evaluate behavioral and other outcomes following adjunctive CBD treatment in individuals with TSC-associated seizures. EpiCom will enroll participants, aged 1–65 years (United States [US]) or 2–65 years (United Kingdom [UK], Canada, and Poland), who are starting CBD for seizures and have moderate/severe behavioral challenges according to the Caregiver Global Impression of Severity scale at screening. Participants will receive CBD (up to 25 mg/kg/d based on individual response and tolerability) in addition to their standard of care (SoC) for 26 weeks, after which participants may choose to continue CBD with SoC or SoC alone for an additional 26 weeks. Key efficacy endpoints include change from baseline on the Aberrant Behavior Checklist (e.g., irritability subscale) and the most problematic behavior on the TAND-Self-Report, Quantified Checklist. Changes in executive function, sleep, QoL, family functioning, seizure outcomes (severity, responder rates, seizure-free days), retention rate, and safety will be evaluated. The trial will enroll ≈75 participants at ≈20 sites across the US, the UK, Canada, and Poland. EpiCom will assess the changes in behavioral and other outcomes associated with TAND and seizure outcomes, including overall symptom severity and treatment retention, following adjunctive CBD treatment in individuals with TSC-associated seizures. The results will inform future studies evaluating pharmacotherapy for behavioral outcomes in similar populations.

## Introduction

Tuberous sclerosis complex (TSC) is a rare genetic disorder that is associated with pathogenic *TSC1* or *TSC2* gene variants, identified in 75%–90% of individuals with TSC, that have been shown to cause upregulation of the mechanistic target of rapamycin (mTOR), which in turn leads to formation of hamartomas in multiple organ systems, including the brain, heart, skin, eyes, kidneys, lungs, and liver [1,2]. Epilepsy is one of the most common neurologic manifestations of TSC, which affects approximately 85% of people with TSC [3]. In addition to seizures, about 90% of people with TSC experience TSC-associated neuropsychiatric disorders (TAND), which include a wide range of behavioral, psychiatric, intellectual, academic, neuropsychologic, and psychosocial manifestations [4–6]. Dysregulation of the mTOR signaling pathway in TSC may contribute to epileptogenesis and neuropsychiatric phenotypes [1,7,8]. Brain abnormalities and epilepsy in individuals with TSC are also implicated in the development of neuropsychiatric problems; coexistence of epilepsy at an early age has been shown to increase the risk of TAND, but neither structural brain abnormalities nor seizures are necessary or sufficient to lead to TAND [9–12].

The “burden of illness” associated with TAND has been identified by families as the greatest clinical burden of TSC, impacting quality of life (QoL) for individuals and their families. Adverse effects on individuals’ QoL include poor sleep, social stigma, social isolation, and depression, with families experiencing excessive financial and healthcare costs, caregiver stress, and employment difficulties [4,6,13]. There are limited treatment options for TAND, with only a handful of studies evaluating the effect of pharmacological or nonpharmacological interventions [4]. Thus, there is a significant need for more evidence-based treatment options for TAND [4,6].

The plant-derived pharmaceutical formulation of highly purified cannabidiol (CBD) is approved as Epidiolex^®^ in the United States (US) for the treatment of seizures associated with Lennox-Gastaut syndrome (LGS), Dravet syndrome (DS), and TSC in patients aged ≥1 year, and as Epidyolex^®^ in the European Union and the United Kingdom (UK) for the treatment of seizures associated with LGS and DS in conjunction with clobazam in patients aged ≥2 years, and as an adjunctive therapy for seizures associated with TSC in patients aged ≥2 years [14,15]. At present, there are limited data that CBD or any other antiseizure medication (ASM) can ameliorate aspects of TAND. However, results from a small cohort of 18 patients with TSC treated under the CBD Expanded Access Program (EAP) [16] and anecdotal reports from the TSC community of patients, caregivers, and healthcare professionals (HCPs) have suggested benefits with CBD treatment in behavioral (e.g., calm or relaxed behavior) and neuropsychological symptoms (e.g., increased attention span, awareness, and concentration) [17]. In the CBD EAP, in addition to reduced seizure frequency after 3 months of adjunctive CBD treatment, cognitive gains such as improvements in alertness, verbal communication, vocalization, and cognitive ability, and initiation of emotional and physical connections were reported in 12 of 14 individuals with parent- and physician-observed global developmental delays [16]. Additionally, behavioral improvements were observed in six of nine individuals with behavioral problems [16]. Behavioral and neuropsychological improvements were noted in individuals who had a reduction in seizure frequency as well as those who did not experience seizure reduction [16]. Thus, although the study was limited by a small sample size, these preliminary results suggest that CBD could be beneficial for the treatment of TAND.

TAND intervention evaluation studies, such as that for CBD, are complicated by the scarcity of instruments available for quantification of behavioral changes associated with TAND and are largely limited to generic instruments, which have limited validation, acceptance, or relevance for TAND [4,6]. Additionally, the TSC population is highly heterogeneous; therefore, the effect of the disorder and the treatments can be highly specific to an individual [5,6,18]. Efforts are underway to develop reliable tools that can be used to specifically evaluate TAND in the real-world setting and in clinical trials. The TAND Self-Report, Quantified Checklist (TAND-SQ), is one such tool that was developed and tested for feasibility and accessibility [19,20] and is currently being validated [21]. It is a quantifiable checklist that can be used by caregivers or individuals with TSC to assess TAND-related challenges as well as an individual’s TAND cluster profile, which includes autism-like behavior, dysregulated behavior, and eat/sleep, mood/anxiety, neuropsychological, overactive/impulsive, and scholastic clusters [6,22]. Identification of TAND clusters can help individuals with TSC and their care providers to plan for further evaluations, treatment, and support [19]. The TSC patient-reported outcome measure (TSC-PROM) for adults was recently evaluated and covers physical and mental functions, activity and participation, and social support aspects of TSC [23].

Given the rarity, complexity, and heterogeneity of TSC and TAND, and vulnerability of affected individuals as well as their caregivers, there is a greater impetus for collaborations among patients, caregivers, and HCPs in clinical trial design to drive interventions with measurable outcomes that are of value to the entire community [4,6,24]. Here we describe the study design of EpiCom (**Epi**lepsy **Com**orbidities; NCT05864846), an interventional, multicenter, open-label, single-arm, phase 3b/4 study, which was designed in collaboration with patient advisory groups (PAGs) and HCPs to evaluate behavioral and other co-occurring outcomes following treatment with adjunctive CBD in individuals with TSC-associated seizures. A primary consideration in designing the study was to evaluate endpoints that provide information on outcomes that can be evaluated in future in-depth clinical trials and are also meaningful to individuals with TSC and their families.

## Materials and methods

EpiCom is an exploratory study that will assess the changes in various outcomes associated with TAND and seizure outcomes, including overall symptom severity and treatment retention, after starting adjunctive CBD treatment in individuals with TSC who experience seizures. Safety outcomes will also be evaluated. The schedule of assessments is presented in **Fig 1**.

**Fig 1 pone.0324648.g001:**
[figure not shown]
Schedule of assessments. ^a^The ED visit is only for participants who wish to discontinue the study and the study intervention (CBD-OS). These participants should initiate a 10-day tapering off of CBD-OS and then complete an end-of-taper visit, followed by a safety follow-up phone call. Participants who withdraw from the study before week 26 should complete assessments scheduled for the 26-week interim review visit, and participants who withdraw from the study after week 26 but before week 52 should complete assessments scheduled for the 52-week final review visit. ^b^Only for participants who wish to discontinue CBD-OS before the end of Treatment Period 1 or Treatment Period 2 but remain on study. These participants should initiate a 10-day tapering off of CBD-OS and then complete an end-of-taper visit, followed by a safety follow-up phone call. For participants who wish to remain on CBD-OS after the study, the 52-week final review visit is the last study visit. ^c^Only for participants who discontinue CBD-OS (after the 26-week interim review visit, 52-week final review visit, EOT visit, or ED visit). ^d^May be a phone call. ABC: Aberrant Behavior Checklist; ABCL: Adult Behavior Checklist; AE: adverse event; ASM: antiseizure medication; ASR: Adult Self Report; BRIEF-2: Behavior Rating Inventory of Executive Function-2; BRIEF-A: Behavior Rating Inventory of Executive Function for Adults; BRIEF-P: Behavior Rating Inventory of Executive Function Preschool; CareGI-S: Caregiver Global Impression of Severity; CBCL: Child Behavior Checklist; CBD-OS: cannabidiol oral solution; CGI-S: Clinician Global Impression of Severity; CSHQ: Children’s Sleep Habits Questionnaire; C-SSRS: Columbia–Suicide Severity Rating Scale; ED: early discontinuation; EOT: end of treatment; PedsQL: Pediatric Quality of Life Inventory; PedsQL FIM: Pediatric Quality of Life Survey Family Impact Module; PGI-S: Patient Global Impression of Severity; PROMIS: Patient-Reported Outcomes Measurement Information System; PSQI: Pittsburgh Sleep Quality Index; SAE: serious adverse event; TAND-SQ: Tuberous Sclerosis Complex-Associated Neuropsychiatric Disorders Self-report Quantified Checklist; WOCBP: women of childbearing potential.

### Co-designing approach for protocol development

The protocol for EpiCom trial was developed in collaboration with the TSC community (**Fig 2**). The process began by identifying HCPs through conference activities, publications, and clinical trials and finding patient and caregiver participants through PAGs at national and international levels. An initial advisory board with PAGs provided feedback on the need to investigate the impact of ASMs on TAND and ways to collaborate with patients and caregivers. Through premeeting surveys, patients and caregivers helped to co-create advisory board topics, including prioritization of TAND elements for evaluation, study design and feasibility, study population, and measurement tool suitability and feasibility. Feedback from the patient/caregiver advisory board was incorporated into the HCP advisory board. Insights (S1 Table) from both advisory boards were then used to design the study. The main aspects of the study design, including the effectiveness endpoints and timing of visits, were created to ensure that the study would measure clinically meaningful outcomes while minimizing participant/caregiver burden. A joint patient-HCP steering group was established and will advise throughout the study period. Input from nine patient organizations from the US and Europe and eight global HCPs was used to design the study protocol.

**Fig 2 pone.0324648.g002:**
[figure not shown]
The process used to co-design the study with the TSC community. HCP: healthcare professional; PAGs: patient advisory groups; TAND: TSC-associated neuropsychiatric disorders; TSC: tuberous sclerosis complex; USA: United States of America.

### Study design

The study consists of three phases (**Fig 3**): screening and baseline period (up to 49 days), 26-week treatment period 1 (adjunctive CBD treatment), and 26-week treatment period 2 (adjunctive CBD or standard of care [SoC]). Each participant will be enrolled in the study for up to 62 weeks, and the overall treatment duration is up to 54 weeks (including an option to taper off CBD at the end of the study if the participant would like to discontinue treatment). At screening, the prospective study participants or their caregivers will sign the informed consent form, followed by eligibility screening conducted up to a 21-day period. During this time, participants/caregivers will also receive training on how to record information in eDiaries. During the 4-week baseline period, participants will complete additional screening and baseline assessments and will be evaluated again for study eligibility.

**Fig 3 pone.0324648.g003:**
[figure not shown]
Study schema. *Participants who decide to discontinue CBD after the 26-week interim review visit but remain on study will form the SoC treatment arm. These participants will taper off CBD and complete a safety follow-up. ^†^Participants who decide to discontinue CBD after the 52-week final review visit will taper off CBD and complete a safety follow-up. For participants who wish to remain on CBD after the study, the 52-week final review visit is the last study visit. CBD: cannabidiol; SoC: standard of care.

During the first 26 weeks of treatment, participants will receive open-label CBD treatment in addition to the SoC. This treatment period consists of the following two phases: a 4-week titration period, during which the CBD dose will be titrated up to the participant’s optimal maximum dose (study site staff will train the participants or caregivers on how to dose and titrate CBD), and a 22-week maintenance period, during which the participants will maintain their optimal dose of CBD. Following a review after the first 26 weeks of treatment, participants will have the option to either continue adjunctive CBD treatment for another 26 weeks or discontinue CBD while maintaining their SoC treatment. Participants who choose to discontinue CBD after a 26-week interim review visit will be gradually withdrawn over a 10-day taper period and complete an end-of-taper visit and a follow-up safety assessment.

Participants who choose to continue treatment with CBD will maintain their dose for the remainder of treatment period 2, until the 52-week final review visit, which will also be the last study visit. Participants who do not continue CBD (outside of the study) after the 52-week final visit will undergo a 10-day taper period and complete an end-of-taper visit and a follow-up safety assessment. Participants will have the option to complete all study visits either at the study site or virtually (e.g., via telehealth or videoconference).

### Study population

Participants, aged 1–65 years in the US or 2–65 years outside the US, will be eligible to enroll if they fulfill the following key inclusion criteria: have a confirmed clinical diagnosis of TSC with a history of seizures in accordance with the 2012 International Tuberous Sclerosis Complex Consensus Conference criteria, which were updated in 2021 [13,25] and have behavioral problems—such as aggression, impulsivity, temper tantrum, self-injury, hyperactivity, extreme shyness, mood swings, poor eye contact, repetitive behaviors, restlessness, difficulty getting along with peers, and rigidity/inflexibility to procedure and/or change—that are considered moderate or severe according to the Caregiver Global Impression of Severity (CareGI-S) at screening. At baseline, prospective participants must have a most problematic behavior score of ≥6 on TAND-SQ to remain eligible. EpiCom participants must either be naive to CBD treatment or must have been off CBD treatment for ≥3 months before screening and taking ≥1 ASM at a stable dose. Concomitant ASMs are allowed, but any modifications or additions are to be avoided in the first 12 weeks, except changes permitted for participant safety reasons.

Prospective participants will be excluded from the study if they had any medical condition that in the investigator’s opinion could affect the study outcomes. This includes significant surgery for epilepsy that in the opinion of the investigator may impact the outcome’s assessment. In addition, participants will be excluded if they have initiation of felbamate within the year before screening, use recreational or medicinal cannabis or synthetic cannabinoid-based medications within the 3 months before screening and are unwilling to undergo a 1-month washout period before rescreening, have significant hepatic impairment, or have any history of suicidal behavior or any suicidal ideation.

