**TAND Outcomes**			
ABC [26,27] A caregiver-reported tool that allows for assessments of problematic behavior in children and adults with developmental disabilities Caregivers will rate the participant’s specific symptoms across the following subscales: irritability, social withdrawal, stereotypic behavior, hyperactive noncompliance, and inappropriate speech	Change from baseline at weeks 13, 26, and 52	Can be used for children and adults Used for assessment in diseases with behavioral problems, including ASD, Down syndrome, and fragile X syndrome [26,28,29] Widely used for evaluating treatment outcomes in autism [30,31,32]	10–15 min
TAND-SQ [19,20] A checklist completed by caregivers or adults^a^ with TSC for assessment of symptoms across TAND-related domains (i.e., neuropsychiatric, cognitive, and behavioral symptoms, psychosocial impact, and overall burden) that can be tracked over time The single most problematic behavior on TAND-SQ for each participant will be identified by the caregiver and the change over time in that behavior will be assessed using an 11-point Likert-type scale Changes in the TAND clusters (scholastic, neuropsychological, ASD-like, dysregulated behavior, overactive/impulsive, mood/anxiety, eat/sleep) and overall NRS TAND-related symptoms will also be evaluated in the study	Change from baseline at weeks 13, 26, and 52	Under validation as part of the TANDem project [21]	20–30 min
CBCL [33,34]/ABCL [35,36] Caregiver-reported questionnaires that examine internalizing behaviors (e.g., depression and anxiety), externalizing behaviors (e.g., aggression), stress, obsessive-compulsive behaviors, and “sluggish cognitive tempo” These questionnaires allow for an assessment of the participant’s behaviors on a 3-point Likert scale	Change from baseline at weeks 26 and 52	CBCL, ABCL, and ASR are components of ASEBA, a widely used and validated measure to assess behavioral, emotional, and social problems and adaptive functioning in individuals of all ages [37] Versions of the CBCL are validated in participants aged 1.5–5 years and 6–18 years CBCL was found to not be as effective as the TAND checklist in detecting neuropsychiatric and psychopathological problems associated with TSC [34] ABCL is validated in participants aged 18–59 years; however, in the current study, it will be used for participants aged 18–65 years	15–20 min

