### TAND outcomes

TAND-specific outcomes will be evaluated using TAND-SQ, which was derived from the TAND Checklist Lifetime Version [20] and is currently being validated by the Global TANDem Consortium [19]. The caregivers will identify the single most problematic behavior and track changes over time through their responses in the TAND-SQ. The trial is designed to assess changes in TAND-associated outcomes that are of importance to the caregivers and individuals with TSC; therefore, the most problematic behavior score is being used to evaluate the caregiver’s impression of change in the problem that is most bothersome to them or the participant, regardless of the severity. Evaluation of the most bothersome symptom has been conducted previously and is recommended by the U.S. Food and Drug Administration for patient-focused drug development [61–63]. Natural TAND clusters—scholastic, neuropsychological, autism spectrum disorder-like, dysregulated behavior, overactive/impulsive, mood/anxiety, and eating/sleeping [22]—will be used to group specific neuropsychiatric characteristics for analysis. Absolute and change from baseline in TAND cluster scores, as measured by average numeric rating scale (NRS), and overall NRS TAND-related symptoms will be summarized at weeks 13, 26, and 52 by using standard descriptive statistics for continuous variables.

Given that the TAND-SQ is a relatively new instrument for assessment of outcomes specific to TSC, it will be complemented by additional well-established tools, such as Aberrant Behavior Checklist [26–32], which caregivers will use to rate the participant’s specific symptoms across the following subscales: irritability, social withdrawal, stereotypic behavior, hyperactive noncompliance, and inappropriate speech. Child Behavior Checklist (CBCL) [33,34], and Adult Behavior Checklist (ABCL) [35,36] or Adult Self Report (ASR) [36] will also be used, as applicable, on the basis of the participant’s age and ability. CBCL, ABCL, and ASR are components of the Achenbach System of Empirically Based Assessment, a validated measure to assess behavioral, emotional, and social problems and adaptive functioning across ages [37]. Changes in the overall severity of behavioral symptoms will be assessed by the caregivers/participants using the CareGI-S/Patient Global Impression of Severity (PGI-S) scale [58] and by clinicians using the Clinician Global Impression of Severity (CGI-S) scale [57,59,60].

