## Discussion

There is an increasing focus on incorporation of “patient experience data” into decision-making for clinical trials and drug development process [63]. Including patient experience information in trial design gives patients a voice and allows for evaluation of endpoints that are of importance to them and their families. The EpiCom study was designed to increase the potential for efficient study execution, data dissemination, and impact on patient care.

In addition to keeping patient and caregiver input at the center of the study design process, EpiCom aims to reduce the burden associated with trial participation by implementing a hybrid decentralized clinical trial (DCT) approach, in which participants will have the choice to attend the clinical trial site, conduct the assessments at home, or both. The DCT strategy allows for clinical trial activities to be conducted at locations other than traditional clinical trial sites, such as the patients’ homes or other locations remote from the clinical trial site (e.g., access to video call visits, home phlebotomy for blood collection, and home delivery of study drug), as well as the use of digital health technologies (e.g., access to assessment tools via their own mobile device or directly on the web). Using the DCT approach, more participants can access the investigational treatment, which in turn can support inclusion of a greater diversity of patient populations and increase efficiency by reducing the burden on caregivers and enhancing engagement among participants, thereby increasing patient recruitment and retention [65].

Highly purified CBD (Epidiolex^®^) is already an approved treatment for seizures associated with TSC in many countries; therefore, because of ethical considerations and based on advice from PAGs, EpiCom was designed as an open-label, single-arm trial to ensure that CBD is available to all eligible participants. The assessment tools were selected primarily on the basis of what the advisory panel members considered the most effective method for measuring outcomes that are of value to the participants of the trial. Other considerations were the validation status of the tools, their previous use in TSC or similar studies, and the time needed to complete the assessments and their complexity.

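### The TAND-SQ score that must be 6 or more for entry is also the baseline of a key endpoint, so regression to the mean biases the uncontrolled change towards improvement by an amount the document cannot fix

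*Protocol article*

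**What the plan says.** All references are to the protocol article.

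- **Entry rule (Study population).** "At baseline, prospective participants must have a most problematic behavior score of ≥6 on TAND-SQ to remain eligible". An earlier severity requirement uses a different instrument: behavioral problems must be "considered moderate or severe according to the Caregiver Global Impression of Severity (CareGI-S) at screening".
- **Endpoint (Abstract; Table 1, TAND-SQ row).** "Key efficacy endpoints include change from baseline on the Aberrant Behavior Checklist (e.g., irritability subscale) and the most problematic behavior" on the TAND-SQ. Table 1 sets the time points at weeks 13, 26 and 52 and says that "the change over time in that behavior will be assessed using an 11-point Likert-type scale".
- **Choice of item (TAND outcomes).** "The caregivers will identify the single most problematic behavior and track changes over time through their responses in the TAND-SQ". The problem tracked is "the problem that is most bothersome to them or the participant, regardless of the severity".
- **Control (Discussion).** "EpiCom was designed as an open-label, single-arm trial to ensure that CBD is available to all eligible participants".
- **Analysis (Statistical analysis).** Change from baseline to week 26 is described with 95% CIs and evaluated in a generalized linear mixed model (GLMM) adjusted for the baseline assessment and age. The study is called exploratory, any P values are nominal, endpoints are not ranked, and no change is to be attributed causally to CBD.
- **Limitations (end of the Discussion).** Response bias, its recalibration over time and caregiver subjectivity are named, with the baseline-adjusted model as mitigation. Regression to the mean is not mentioned.

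**The concern.** One rating does two jobs. It decides who stays in the study, and it is the value from which change is measured. The article describes no second rating between qualification and first dose.

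Any rating with imperfect repeatability contains a transient part. Keeping only people who score 6 or more keeps, on average, people whose transient part was positive that time. It does not recur at follow-up, so the mean falls without any effect of treatment. In a controlled trial the fall would occur in both arms and cancel. Here nothing cancels it before week 26.

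The study is meant to inform the endpoints of future trials. If part of the mean change comes from the entry rule, both the apparent responsiveness of this item and the effect size carried forward are inflated, and a reader cannot tell by how much.

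**Working it through.** **The plan's own figure.** 75 enrolled with 20% withdrawal gives 75 × (1 - 0.20) = 60 evaluable at week 26, as the Sample size section states. No effect size, SD, power or alpha is given.

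**Inputs from the document.** Cut-off of 6 or more at baseline; 11-point scale, taken as 0 to 10 with higher meaning worse; 60 evaluable; no control to week 26.

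**Assumptions, because the document gives no figures.** Mean μ and SD σ of the score among candidates before the cut, and correlation ρ between two ratings of the same person with no true change. Ranges: μ 5 to 8, σ 1.5 to 2.5, ρ 0.5 to 0.9.

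**Step 1, formula.** Under a normal approximation, with 5.5 as the continuity-corrected cut:

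- a = (5.5 - μ)/σ and λ = φ(a)/(1 - Φ(a))
- mean qualifying score = μ + σλ
- mean of any later rating = μ + ρσλ
- expected change = -(1 - ρ)σλ, which is below zero whenever ρ < 1

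**Step 2, one case.** μ = 6, σ = 2, ρ = 0.7: a = -0.25 and λ = 0.646. The mean qualifying score is 6 + 2 × 0.646 = 7.29. The mean later score is 6 + 0.7 × 2 × 0.646 = 6.90. The expected change is -0.39.

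**Step 3, simulation on the rounded 0 to 10 scale.** The same case gives -0.41 points with an SD of change of 1.48. With n = 60 the 95% CI half-width is 2.00 × 1.48/√60 = 0.38. The chance that the CI lies wholly on the improvement side is 56% to 58%, depending on the approximation, against a nominal 2.5%. Without the cut the expected change is 0.00.

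**Step 4, the range.**

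| μ | σ | ρ | Expected change | Chance that CI shows improvement |
|---|---|---|---|---|
| 5 | 2.5 | 0.5 | -1.19 | about 99% |
| 5 | 2 | 0.7 | -0.62 | about 90% |
| 6 | 2 | 0.5 | -0.67 | about 82% |
| 6 | 2 | 0.7 | -0.41 | 56% to 58% |
| 6 | 2 | 0.9 | -0.16 | about 25% |
| 7 | 2 | 0.7 | -0.25 | about 27% |
| 8 | 2 | 0.7 | -0.13 | about 11% |
| 8 | 1.5 | 0.9 | -0.02 | about 4% |

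The first and last rows are the extremes of the full grid for expected change.

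**Step 5, baseline adjustment.** Write the model as change = α + β(baseline - mean baseline). Then α is the mean change at the average baseline, and that is the quantity in Step 1. The slope β absorbs differences between participants around that average; it leaves α where it was. Adjustment for age does not alter this.

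**Step 6, a separate baseline.** If a second rating taken after qualification is the reference, and its error is independent of the first, its mean is μ + ρσλ. The follow-up rating has the same mean, so the expected change is 0. Simulation agrees (0.00 at the settings above).

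**The case against.** Four points can be made for the plan.

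**The claims are modest.** The Statistical analysis section calls the study exploratory and P values nominal, and rules out causal attribution because there is no control. This stands as a limit on the consequence. It does not correct the estimate: a purely descriptive mean change and its CI are still shifted, and the reader is not told that the entry rule helped to produce the change.

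**The effect may be negligible.** Candidates have already been screened for moderate or severe problems on CareGI-S, and the item is each person's most problematic behavior. If most candidates score well above 6, the cut removes few of them; at a mean of 8 and SD of 1.5 the shift is below 0.1 points. This stands, and it is why no single figure can be given.

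**A reader might infer that the cut-off contradicts the statement that the tracked problem is** "the problem that is most bothersome to them or the participant, regardless of the severity". It does not. That sentence explains which problem is followed, namely the most bothersome one; it says nothing about who may enter. A floor of 6 on the chosen item is compatible with it.

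**A reader might also infer that the behavior is picked as the highest-scoring one on the day, which would add to the bias.** The document says only that the caregiver identifies the most problematic behavior, and it ties that choice to bother. Selection on the rating itself is possible but not stated, and the figures above leave it out.

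**Conclusion.** The point holds for direction, not for a particular size. The qualifying score is the baseline of a key endpoint, there is no concurrent control to week 26, and with any reliability below 1 the expected change under no effect is an improvement. Neither the baseline-adjusted model nor the caveat on causality removes this from the estimate or its 95% CI.

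The size rests wholly on the assumed mean, SD and reliability: from negligible to more than 1 point, with about 0.4 points in the middle case. It would be wrong to say that the study will show a significant improvement for this reason alone, because at the favorable end of the range the chance is barely above the nominal 2.5%.

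The week-52 comparison of CBD with standard of care is less affected, since both groups passed the same cut, though participants choose their own group.

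**What to change.** **Participants not yet dosed.** Use the qualifying rating for eligibility only. Re-ask the single 11-point item, for the same behavior, before the first dose and make that the analysis baseline. The cost is one extra eDiary item and, probably, a smaller reported improvement. Some bias remains if the two ratings share error, for example through recall or a bad spell lasting weeks. The article expected the last patient in during the first quarter of 2025, so this may reach few participants.

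**Participants already enrolled.** No new data are needed:

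- Beside the observed change, print the change expected from regression to the mean for the cut-off of 6, over a stated reliability range and with the assumed mean and SD shown.
- Name this as a limitation of the endpoint, and do not present baseline adjustment as a remedy for it.
- Read the result alongside ABC irritability, which is not an entry criterion. It should not be promoted to lead endpoint: the plan assigns no ranking, and because caregivers rate both instruments, shared rating error could carry part of the selection effect into ABC.

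The cost for this group is analysis-plan and reporting text only.
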